### Randomization

To evaluate the feasibility of healthcare provision via telemedicine in MSA settings, recruited individuals with MSA are 1:1 block-randomized to receive either personalized best medical care with integrated mobile palliative interventions as needed (n = 23) OR personalized best medical care (including on demand mobile palliative interventions) PLUS telemedicine (n = 23). The randomization has a 2-strand stratification that accounts for the early (i.e., able to walk) versus advanced (i.e., wheel-chair bound) stage of MSA at the time of recruitment. The randomization sequence is kept concealed to the recruiting doctor until the baseline assessment is completed.

### Analysis sets and subgroups

For the primary objective (see Table 1), we will compare the prospectively recruited MeDeMSA Care cohort with data from the historical EMSA-SG cohort (Wenning et al. 2013), matched by age (± 5 years), sex, and disease duration (± 12 months). Disease duration is defined as the time from the onset of motor symptoms or selected autonomic features, including orthostatic hypotension, urinary urge incontinence, or incomplete bladder emptying. If exact matching is not possible due to unavailable controls, an alternative matching approach by categorizing individuals into subgroups based on age (< 60 versus ≥ 60 years) and disease duration (< 3 vs. ≥ 3 years) will be applied. To better characterize the MeDeMSA Care cohort and, secondarily, enable detailed comparisons between personalized best medical care with and without telemedicine, the EQ-5D-5L tool has been chosen for the present study (Janssen et al. 2013; Feng et al. 2021). This offers five response levels: no/slight/moderate/severe/extreme problems. For comparisons with the historical cohort, which used the EQ-5D-3L with three response levels (no/moderate/extreme problems), EQ-5D-5L responses will be grouped post-hoc and consistently applied across assessments (van Hout et al. 2012).

For secondary objectives (see Table 2), the MeDeMSA Care cohort will be divided into early versus advanced MSA (i.e., wheelchair-bound at the time of recruitment), and further sub-grouped by sex (male versus female), MSA phenotype [parkinsonian versus cerebellar (Wenning et al. 2022)], age (< 60 versus ≥ 60 years), and disease duration (< 3 vs. ≥ 3 years) for exploratory purposes.

To explore the impact of telemedicine on various outcomes (QoL, symptom progression, complications, caregiver burden, costs, and individual satisfaction with the personalized treatment plan), exploratory comparisons will be made between the subgroup of individuals randomized to receive personalized best medical care and individuals receiving personalized best medical care PLUS monthly and on-demand telemedicine consultations, as well as between each of these subgroups and the historical EMSA-SG cohort.

The individual healthcare preferences, psychological counselling needs, as well as the feasibility and barriers to mobile palliative care in MSA settings will be analyzed in a descriptive way. Subgroup analyses will be performed depending on the available sample size for the different subgroups (i.e., sex, MSA phenotype, younger versus older age, and shorter versus longer disease duration) upon study completion.

### Data analysis

The distribution of quantitative data will be assessed using the Shapiro–Wilk test. Quantitative variables will be reported as mean (± SD) for normally distributed data or median (interquartile range, IQR) for non-normally distributed data, and qualitative variables as counts (percentages). Qualitative variables will be compared using Pearson’s Χ^2^ test (or Fisher’s exact test, if n < 5) and quantitative variables using the Mann–Whitney U or t-test, depending on the data distribution. A Benjamini–Hochberg correction will be applied for multiple tests, whenever appropriate. Binary logistic regression with a receiver operating characteristics (ROC) area under the curve (AUC) calculation will follow univariate analysis when applicable.

Changes in EQ-5D, motor, and non-motor scores between the MeDeMSA Care cohort and age-, sex-, and disease duration-matched historical EMSA-SG individuals will be evaluated with ANOVA for repeated measurements or linear mixed models, as most appropriate. Comparisons between randomization groups and the historical cohort will be run on a descriptive basis, with post-hoc tests adjusting for type-1 error based on ANOVA results.

QoL and caregiver burden changes in caregivers of MSA individuals receiving personalized best medical care with or without telemedicine will be analysed with ANOVA or linear mixed models, adjusted for the disease stage of the cared-for individual with MSA. Correlation analyses will assess the relationship between the caregivers’ QoL and burden with the disease characteristics (e.g., symptom constellation and severity) of the cared-for individual with MSA.

Statistical analysis will be performed with SPSS version 30.0.0 or future releases. P values below 0.05 will be considered statistically significant, with 95% confidence intervals considered where appropriate.

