	To assess whether monthly multidisciplinary telemedicine visits in addition to a multidisciplinary, personalized treatment plan including mobile palliative care - Attenuate the baseline to 6-, 12- and 18-months QoL worsening - Attenuate the progression of motor and non-motor MSA symptoms, including time to clinical milestones in prospectively recruited MSA individuals compared to sex-, age- (± 5 years), and disease duration-(± 12 months) matched MSA individuals from the historical EMSA-SG cohort^a^ and to prospectively recruited MSA individuals receiving in-person visits and mobile palliative care (as needed) only	- Baseline to 6- and 12-months EQ-5D-5L score change - Baseline to 6-, 12- and 18-months changes in the MSA-QoL total score and subscores - Baseline to 6-, 12- and 18-months change in motor and non-motor scales (total and subscores, including video-based, rater-blinded assessment of the UMSARS motor subscore and Hoehn & Yahr stage) - Time to clinical milestones (i.e., falls at least once a day, feeding by nasogastric tube or gastrostomy, unintelligible speech, indwelling catheter, wheelchair dependency)
	To assess whether monthly multidisciplinary telemedicine visits in addition to a multidisciplinary, personalized treatment plan including mobile palliative care - Reduce the number of medical complications - Reduce the caregiver burden - Provide an advantage in terms of benefit-harm and cost-effectiveness tradeoffs - Increase the individual satisfaction with the personalized treatment plan over the 18-months study period in prospectively recruited MSA individuals compared to prospectively recruited MSA individuals receiving in-person visits and mobile palliative care (as needed) only	- Number of medical complications (i.e., falls with or w/o injuries, urinary tract infections, choking, aspiration pneumonia, hospitalizations, death and others) over the 18-months study period - Baseline to 6-, 12- and 18-months change in the EQ-5D-5L score of informal caregivers of prospectively recruited MSA individuals - Baseline to 6-, 12- and 18-months change in PQoL Carers score and other caregiver-burden indicators in informal caregivers of prospectively recruited MSA individuals - Baseline and 12-months semi-structured online interview - Single-intervention and cumulative healthcare costs over the 18-months study period - Month 1 to 7, 13 and 18 SAPS change

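### A Shapiro–Wilk pre-test decides whether means or ranks are compared for outcomes outside the ANOVA or mixed-model sentences, and the article names no baseline or stage covariate for patient scores between the randomised arms

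*Protocol article*

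**What the plan says.** In the Data analysis section, "The distribution of quantitative data will be assessed using the Shapiro–Wilk test". The result sets the summary, which is a mean with SD or a "median (interquartile range, IQR) for non-normally distributed data". It also sets the test, since the same paragraph compares "quantitative variables using the Mann–Whitney U or t-test, depending on the data distribution".

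Three later sentences in that section go beyond this general rule:

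- Changes in EQ-5D, motor and non-motor scores against the matched historical cohort, the primary outcome among them, "will be evaluated with ANOVA for repeated measurements or linear mixed models, as most appropriate"; the general rule is not used for these.
- On the two telemedicine arms, the next sentence reads: "Comparisons between randomization groups and the historical cohort will be run on a descriptive basis, with post-hoc tests adjusting for type-1 error", and it ties the adjustment to what the ANOVA shows.
- Caregiver quality of life and burden by telemedicine arm "will be analysed with ANOVA or linear mixed models, adjusted for the disease stage of the cared-for individual with MSA".

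Under Randomization, 23 patients are allocated to each arm. "The randomization has a 2-strand stratification that accounts for the early" versus advanced stage of disease. Table 1 lists "Single-intervention and cumulative healthcare costs over the 18-months study period" among the telemedicine outcomes, alongside a cost-effectiveness objective. The section on analysis sets and subgroups calls the comparisons between arms exploratory and includes costs among them.

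**The concern.** A t-test compares means and a Mann–Whitney test compares ranks, so they answer different questions. Under the general rule the observed sample chooses the question. Many outcomes in Table 1 recur at several visits. Any of them left to the general rule could be reported as a mean difference at one visit and as a median with a rank test at the next.

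Costs are the clearest case. Cost-effectiveness rests on the difference in mean cost. Cost data are usually right-skewed, so a normality gate tends to send them to the rank test.

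The only randomised contrast in the study is small. Baseline scores and stage are recorded for every patient, and a model using both would sharpen that contrast without new data. The article specifies stage adjustment for caregivers by arm and names no such adjustment for the patients themselves.

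**Working it through.** The article gives no sample size or power for the randomised comparison. Its total of 46 is derived for the comparison with the historical cohort, so there is no plan figure to reproduce here.

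**Inputs from the article.** 23 patients per arm (Randomization). Dropout of 10%, a difference of 0.08, an SD of 0.25 and a significance level of 5% (Sample size calculation). Evaluable patients per arm: 23 × 0.90 = 20.7, about 21. Standardised effect: 0.08 / 0.25 = 0.32 SD. The test is taken as two-sided, which the article does not state.

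**Assumed inputs, not in the article.** The correlation r between baseline and follow-up, the shape of the cost distribution, and the outcome difference between stages.

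**1. Switching by chance.** If each arm is tested at 5% and the data are normal, the probability that at least one arm is rejected is 1 − 0.95² = 0.0975. A simulation at 21 per arm gives 9.4%. With moderately skewed data (gamma), 33–38% of comparisons switch. Choosing the test this way left type I error at 4.5% for normal data with identical arms.

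**2. Costs.** With lognormal costs and 23 per arm, Shapiro–Wilk rejects in a single arm as follows:

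| Coefficient of variation (assumed) | Rejection by Shapiro–Wilk |
|---|---|
| 0.53 | 60% |
| 0.95 | 89% |
| 1.31 | 96% |

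To see what the rank test then measures, take log-scale SDs of 0.6 and 1.0 in the two arms:

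- Equal medians: the ratio of means is exp(1.0²/2) / exp(0.6²/2) = exp(0.32) = 1.38. Mann–Whitney rejects in 5.5% of trials, so a 38% difference in mean cost is hardly seen.
- Equal means: the ratio of medians is exp(−0.32) = 0.73. Mann–Whitney rejects in 24% of trials although mean costs do not differ.

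**3. Baseline adjustment.** With σ the SD of a single score, the residual variance after adjusting for baseline is σ²(1 − r²), and the variance of a change score is 2σ²(1 − r). Their ratio is (1 + r)/2. At r = 0.3 it is 0.65, a 35% reduction. At r = 0.8 it is 0.90, a 10% reduction.

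Power for 0.08 at 21 per arm, taking 0.25 as the SD of final values:

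| r (assumed) | Change score | Baseline-adjusted |
|---|---|---|
| 0.4 | 15% | 20% |
| 0.6 | 21% | 24% |

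At 20.7 per arm and r = 0.8, adjusted power reaches only about 40%.

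**4. Stage adjustment.** For two strata of equal size that differ by d within-stratum SDs, the variance used by an unadjusted test is 1 + d²/4 times the stage-adjusted variance. This gives 1.06, 1.25 and 1.56 for d = 0.5, 1.0 and 1.5 (assumed).

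**The case against.** The strongest reply is that the general rule reaches less far than its wording suggests. Score changes against the historical cohort, including the primary outcome, go to repeated-measures ANOVA or mixed models. The following sentence, on randomisation groups and the historical cohort, uses ANOVA-based post-hoc tests and may cover scores between the arms as well. This stands. A reader might infer that the pre-test governs the main scales or the primary analysis, and the text does not support that.

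A reader might also infer that the patient analyses ignore baseline altogether. They do not: most telemedicine outcomes in Table 1 are changes from baseline. What remains is the narrower difference in efficiency between a change score and a baseline-adjusted model.

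Nor does the article say that costs will be compared by ranks. That follows only if the general rule is applied to costs and Shapiro–Wilk rejects. The decision-analytic model has its own section and is free to use mean costs from the same patient data.

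A large power gain is a further tempting reading. With an effect of 0.8 SD and r = 0.4, power rises from about 65% to 78%. That effect is 2.5 times the article's own 0.32 SD, and the gain comes from replacing change scores with adjustment. Removing the gate alone leaves power unchanged for normal data (63.8% with the gate, 63.9% without).

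Finally, the comparison is exploratory, and a condensed article may leave covariates to a fuller document. This weakens the point on covariates. It does not weaken the point on the pre-test, which the article itself states.

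**Conclusion.** The point holds within limits. The stated pre-test rule is a poor choice for every outcome that falls under it: about 10% of comparisons of normal data would switch to ranks by chance, and under moderate skew the choice remains partly a matter of chance. If the rule is applied to costs, a rank comparison is likely and would not answer the question about mean cost. This rests on the assumption of skewed costs.

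The lack of a named baseline or stage covariate for patient scores between arms is a smaller matter. It sits oddly beside the stratified randomisation and the stage-adjusted caregiver analysis, but it is not a contradiction. The gain from adjustment is a 10–35% lower variance than change scores for r from 0.8 down to 0.3, and r is assumed. No choice of analysis makes about 21 per arm adequate for a difference of 0.08.

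The primary historical comparison and the type I error are not at issue. The cost is in interpretation and, to a lesser degree, in the precision of an exploratory contrast.

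**What to change.** Remove the Shapiro–Wilk gate and fix one method per outcome in advance.

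- **Patient scale scores between randomised arms:** a linear or mixed model with the baseline score and early/advanced stage as covariates, reporting the mean difference with a 95% confidence interval (bootstrap if residuals are skewed).
- **Costs:** the difference in mean cost between arms with a bootstrap confidence interval. Medians may be added as description.
- **Rank tests:** only for outcomes named in advance, such as the single 0–10 satisfaction ratings.
- **Scope:** one sentence stating which outcomes each method covers, so that it is clear whether the ANOVA-based post-hoc wording applies to scores between the arms.

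The change is to analysis wording and needs no new data. Its downside is slightly more analysis work.

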### Population

We plan to recruit 46 individuals, who fulfill all the inclusion criteria listed below:i.Age ≥ 30 years at the time of consent;ii.Diagnosed with clinically probable OR clinically established MSA according to the current criteria of the International Parkinson Disease and Movement Disorder Society (Wenning et al. 2022);iii.Life-expectancy of at least 24 months as assessed by the investigator at the time of consent;iv.Understands and agrees to comply with the study procedures and provides written informed consent (Note: a legal representative may NOT provide consent on behalf of the subject);v.Signed and dated informed consent document;vi.Fluency in German;vii.If unable to walk or stand without assistance/support at the time of consent, the participant must live in Tyrol or in another Austrian region with available mobile palliative care.

Candidates are excluded from the study if they meet any of the following conditions:i.Participation in an interventional clinical study at screening and throughout the study that would interfere with the MeDeMSA Care personalized treatment plan or would not permit telemedicine or mobile palliative care;ii.Charlson Comorbidity Index > 4 at the time of consent;iii.Other major underlying medical conditions that may confound interpretation of study results as assessed by the investigator.

We further plan to recruit up to 46 informal caregivers of individuals with MSA participating in the MeDeMSA Care trial, provided they meet the following inclusion criteria:i.Informal caregiver (i.e., a person not receiving payment for caregiving, except for care allowances and tax return schemes available in Austria) of an individual with MSA recruited in the present study;ii.Life-expectancy of at least 24 months, as assessed by the investigator at the time of consent;iii.Aged 18 or older at the time of consent;iv.Understands and agrees to provide information as outlined in the study protocol and to engage in semi-structured online interviews;v.Provides signed and dated written informed consent;vi.Full legal capacity;vii.Fluency in German.

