## Statistics

### Sample size calculation

The sample size for the present study has been estimated based on data of the EMSA-SG natural history study (Wenning et al. 2013). In this historical cohort, individuals with MSA showed an average EQ-5D score at baseline of 0.35 (95% CI 0.27–0.42), which worsened to 0.17 (95% CI 0.06–0.28) over an observational period of 18 months under standard care (Wenning et al. 2013). In other chronic medical conditions, treatment is considered to be positively associated with QoL, if the EQ-5D score change in the interventional group averages 0.08 points above that of the control group at follow-up (Kwakkenbos et al. 2013). If effective, we therefore estimate the MeDeMSA Care program to limit the baseline to 18 months EQ-5D worsening to 0.25 (± 0.25 standard deviation, SD) in the MSA individuals receiving personalized best medical care with integrated mobile palliative and telemedicine support, as needed. With an assumed significance level of 5% and a power of 80%, 46 individuals with MSA should therefore enroll in the trial to observe an effect of the personalized multidisciplinary care program compared to the standard care offered to the historical MSA cohort, including an expected drop-out rate of 10% over the study course.

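### If the logistic models take their variables from the univariate tests and the AUC comes from the same roughly 41 patients, any AUC reported will be optimistic

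*Protocol article*

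**What the plan says.** The Data analysis section first lists the two-group tests (chi-squared or Fisher, t-test or Mann–Whitney). It then says "A Benjamini–Hochberg correction will be applied for multiple tests, whenever appropriate", and next "Binary logistic regression with a receiver operating characteristics (ROC) area under the curve (AUC) calculation will follow univariate analysis when applicable". It names no binary outcome, candidate list, rule for entering variables or analysis set for these models, and it does not say whether the AUC is corrected for optimism.

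On numbers, the Population section states "We plan to recruit 46 individuals", and the Sample size calculation section describes that total as "including an expected drop-out rate of 10% over the study course". The primary comparison with the historical cohort is planned separately, by repeated-measures ANOVA or linear mixed models.

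**The concern.** An AUC computed on the patients who were used to choose and fit a model measures fit, not prediction. With a small sample and many possible predictors, the difference is large. The legend of Fig. 1 lists more than twenty scales and tests, and Table 1 adds subscores and repeated time points, so a long candidate list is possible. In 41 patients the smaller outcome group cannot exceed 20.

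At stake is how a secondary result is read. An AUC in the low to mid 0.70s would usually be taken as useful discrimination. Here it may be what noise produces, and the usual confidence interval would seldom reveal this.

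**Working it through.** **Inputs from the document.** 46 patients and 10% drop-out: 46 × 0.9 = 41.4, so about 41 evaluable; in reverse, 41/0.9 = 45.6, rounded up to 46. The significance threshold is p < 0.05. The article states no AUC, so there is no planned AUC to reproduce. How 46 was derived is a separate matter and does not enter here.

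**Assumptions, because the document gives no figure.** The univariate step selects at p < 0.05. There are 1 to 30 candidate predictors, independent and normally distributed. The outcome is present in 20 or 10 of 41 patients. A pooled analysis with matched controls has 41 + 41 = 82. No predictor has any effect, so the true AUC is 0.50.

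**Step 1: the smallest AUC that passes the screen.** For one predictor the t-test is significant when the standardised difference d exceeds t × √(1/n₁ + 1/n₂). For normal data the AUC is Φ(d/√2).

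- 20 v 21: d = 2.023 × 0.3124 = 0.632; AUC = Φ(0.447) = 0.67
- 10 v 31: d = 2.023 × 0.3637 = 0.736; AUC = Φ(0.520) = 0.70
- 41 v 41: d = 1.990 × 0.2209 = 0.440; AUC = Φ(0.311) = 0.62

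A predictor that passes the screen at n = 41 therefore starts at an AUC of roughly 0.67 to 0.70, whatever the truth. Averages must lie above that.

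**Step 2: how often a noise model is reached.** For k independent candidates the chance that at least one passes is 1 − 0.95^k: 5% (k = 1), 23% (5), 40% (10), 64% (20), 79% (30). Benjamini–Hochberg at 0.05 holds this near 5% for any k when nothing is related to the outcome.

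**Step 3: simulation.** Each run applied t-test selection, a logistic fit and an AUC on the same patients, with 600 runs per cell; the 30-candidate row comes from a separate set of 2,000 runs. A dash means the cell was not in those runs.

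| Candidates, p < 0.05 | Model fitted | Mean AUC, 20 of 41 | Mean AUC, 10 of 41 | Mean AUC, n = 82 |
|---|---|---|---|---|
| 1 | about 5% | 0.71 | 0.72 | 0.65 |
| 5 | about 23% | 0.72 | 0.74 | 0.65 |
| 10 | about 40% | 0.72 | 0.76 | 0.66 |
| 20 | about 62% | 0.74 | 0.78 | 0.68 |
| 30 | about 79% | 0.77 | – | – |

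The model-fitted column is for n = 41; at n = 82 it is nearly the same. Means are over runs in which a model was fitted. With 30 candidates at n = 82 the mean is about 0.69. At n = 41 a standard 95% interval excluded 0.5 in about 76 to 93% of the fitted noise models with 1 to 20 candidates.

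**Step 4: with Benjamini–Hochberg at n = 41.** A noise model is fitted in about 4 to 8% of runs, and its mean AUC is then 0.71 to 0.83. Counting 0.50 for every run without a model, the overall average is 0.51 to 0.52.

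**Step 5: no screen, all named predictors entered at n = 41.** Mean AUC is 0.57 to 0.59 with one predictor, about 0.61 to 0.70 with two to four, 0.70 to 0.72 with five, and 0.79 to 0.82 with ten.

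**The case against.** The strongest reply is that the article never calls the univariate step a screen. Its sentence also fits descriptive comparisons followed by a model with clinically chosen covariates. That stands, and the point is therefore conditional. It does not remove the problem, because Step 5 shows that an uncorrected AUC from two to five unscreened predictors is still optimistic.

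Second, predictor lists and internal validation commonly sit in an analysis plan or full protocol, neither of which is shown. That also stands: their absence here is not an error. What can be assessed is the stated sequence and what it yields if nothing is added.

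Third, a reader might infer that this procedure reports an AUC well above 0.5 whenever no predictor works. The figures do not support that. The inflation applies once a model is fitted. With few candidates, or with Benjamini–Hochberg applied, most null analyses yield no model and no AUC. Because the correction is to be used only when judged appropriate, whether it covers this step is open, so both cases are shown.

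Fourth, a reader might infer that the trial's conclusions or its policy recommendations rest on these models. No objective in Table 1 is a prediction model. The Future directions section ties its policy aims to feasibility, quality of life and health-economic results. The telemedicine and subgroup comparisons are already called exploratory.

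Finally, independent predictors are a simplification: the scales overlap in what they measure, so the effective number of candidates may be smaller than their count.

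**Conclusion.** The point holds in conditional form and is minor. If variables are carried forward at p < 0.05 and the AUC is taken from the same 41 or so patients, noise alone gives an average of about 0.71 to 0.77 when a model is fitted (5 to 30 candidates, near-even split). The average is slightly higher with 10 events (0.74 to 0.78 for 5 to 20 candidates) and about 0.65 to 0.69 in a pooled set of 82. Such a model arises in about 20 to 80% of analyses without Benjamini–Hochberg and about 4 to 8% with it. The correction governs the frequency and leaves the AUC of a fitted model uncorrected. The candidate count, event share, analysis set and selection rule are all assumptions. The primary comparison is unaffected.

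**What to change.** State in the analysis plan that, for each binary outcome, a small number of predictors is chosen on clinical grounds. Whether or not any screening is used, report a bootstrap optimism-corrected AUC with its interval, and repeat any selection step in every resample. Naming a few predictors is not enough without the correction, because two to four still show about 0.61 to 0.70 under no effect. Label the resulting models hypothesis-generating.

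The cost is a few sentences, some programming and a less favourable AUC. At the March 2025 manuscript revision 23 of the 46 patients had been recruited, so at that point the wording could still be settled ahead of the final analysis.

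### Controls are selected by matching on sex, age and disease duration, but the primary analysis as named includes neither the matched set nor the matching variables

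*Protocol article*

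**What the plan says.** Table 1 and Analysis sets and subgroups define the primary comparator as EMSA-SG individuals of the same sex, within 5 years of age and within 12 months of disease duration. The fallback is looser: "If exact matching is not possible due to unavailable controls, an alternative matching approach by categorizing individuals into subgroups", namely below versus at or above 60 years and below versus at or above 3 years of disease. No matching ratio is stated, nor whether one historical individual may serve several patients.

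Under Data analysis, changes in EQ-5D and in motor and non-motor scores between the cohort and its matched "historical EMSA-SG individuals will be evaluated with ANOVA for repeated measurements or linear mixed models, as most appropriate". No term for the matched set and no covariate is named. The caregiver model in the same section does carry a named adjustment, for the disease stage of the cared-for person.

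The randomised arms are also compared with each other, "as well as between each of these subgroups and the historical EMSA-SG cohort". Data analysis calls these comparisons descriptive, and Table 1 (telemedicine objective) describes their historical comparator as matched.

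**The concern.** Matching makes each patient and the corresponding control resemble each other on characteristics that may predict progression. An analysis that takes no account of this can misstate the standard error of the between-cohort difference, in a direction that depends on how the matching was done:

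- With 1:1 matching and distinct controls, a positive correlation within pairs makes the unmatched standard error too large. The test is conservative and the precision gained by matching is not used.
- If a historical individual serves several patients and is counted as a separate observation each time, the standard error can be too small.
- Under the coarse fallback, two people in the same class may still differ widely in age or duration, and nothing in the named model adjusts for that.

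At stake is the precision and calibration of the primary endpoint in a study with about 41 completers.

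**Working it through.** **Inputs from Sample size calculation.** Difference 0.08 ("averages 0.08 points above that of the control group at follow-up"; 0.25 against 0.17). SD 0.25, from "worsening to 0.25 (± 0.25 standard deviation, SD". 46 enrolled with 10% drop-out: 46 × 0.9 = 41.4, about 41 completers. "P values below 0.05 will be considered statistically significant" (Data analysis) gives no sidedness, so two-sided 5% is assumed.

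**The plan's own figure.** "With an assumed significance level of 5% and a power of 80%, 46 individuals with MSA should therefore enroll". For two independent groups, n = 2(1.96 + 0.842)² × 0.25² / 0.08² = 153.3, so 154 per group. A paired or one-sample reading with SD 0.25 for the difference halves this to 76.7, so 77. Neither gives 41 completers or 46 enrolled. That is a separate problem. Here the inputs serve only to size the matching question.

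**Assumptions.** The within-set correlation ρ of the 18-month change is not in the article; 0 to 0.5 is shown. The SD of 0.25 is taken as the SD of the change. The comparison is reduced to one time point and a two-sample against a paired test, as a proxy for the named models.

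**Formula.** Let each control serve k patients, with n patients, n/k distinct controls, and all members of a set sharing correlation ρ. Then:

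- true variance of the difference = (σ²/n)[1 + (k − 1)ρ + k − 2kρ] = (k + 1)(1 − ρ)σ²/n
- variance assumed by an unmatched test on n against n rows = 2σ²/n
- ratio, true to assumed = (k + 1)(1 − ρ)/2
- actual type I error = 2[1 − Φ(1.96/√ratio)]

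**1:1 without reuse (k = 1): ratio = 1 − ρ.** The unmatched standard error is 0.25 × √(2/41) = 0.0552, and 0.08/0.0552 = 1.449. Unmatched power is Φ[(1.449 − 1.96)/√(1 − ρ)]; matched power is Φ[1.449/√(1 − ρ) − 1.96]. Simulated values (41 pairs, 40,000 runs, t-tests) are in brackets.

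| ρ | Type I error, unmatched | Power, unmatched | Power, matched |
|---|---|---|---|
| 0 | 5.0% (5.0%) | 30% (30%) | 30% (29%) |
| 0.1 | 3.9% (4.0%) | 29.5% (29.4%) | 33.3% (32.7%) |
| 0.2 | 2.8% (3.0%) | 28.4% (28.2%) | 36.7% (35.4%) |
| 0.3 | 1.9% (2.0%) | 27.1% (26.5%) | 41.0% (39.3%) |
| 0.5 | 0.6% (0.6%) | 23.5% (23.1%) | 53.5% (51.6%) |

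The simulated power loss is about 3, 7 and 13 points at ρ = 0.1, 0.2 and 0.3.

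**Each control used twice (k = 2): ratio = 1.5(1 − ρ).** At ρ = 0, 1.96/√1.5 = 1.60, giving 11.0%. At ρ = 0.1, 0.2 and 0.3 the formula gives 9.2%, 7.4% and 5.6%. Simulation with 40 patients sharing 20 controls gives 11.3%, 9.3%, 7.7% and 5.8%. The ratio reaches 1 at ρ = 1/3; above that the test is conservative again.

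**Could reuse arise?** The historical result is "which worsened to 0.17 (95% CI 0.06–0.28) over an observational period of 18 months under standard care". If that is a simple interval for a mean, its standard error is (0.28 − 0.06)/(2 × 1.96) = 0.056. At SD 0.25 this corresponds to (0.25/0.056)², about 20 individuals; at SD 0.30 about 29; at SD 0.35 about 39. An SD of about 0.36 would be needed for 41. So the pool with 18-month EQ-5D may be small relative to 41 completers. This is an inference from one interval and an assumed SD, and does not show that controls will be reused.

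**The case against.** The strongest reply is that a reader might infer that the plan treats the cohorts as independent and discards the matching, and the article says neither. It calls the comparators matched, both model families can carry a matched-set effect, and random-effect structure is commonly left to a full protocol or SAP that is not shown. This stands: the stronger reading is an inference from silence. What remains is that the model as stated lacks the terms its design calls for, while an adjustment is named for the caregiver model.

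A reader might also infer that the primary test would produce too many false positives. With 1:1 matching and no reuse it would do the opposite. Inflation requires reuse, which the article does not state.

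The size rests on an assumed ρ. Sex, age and duration may predict 18-month change only weakly, and at ρ = 0.1 the gain is about 3 points. Individual pairs are not assured either: under the fallback there may be no natural pair, and covariate adjustment is then the counterpart of a pair term.

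Finally, the arm-versus-historical comparisons might seem to lose their balance because each arm meets controls matched to the other arm's patients. That is minor. The comparisons are descriptive, the arms are randomised, so controls matched to the whole cohort are balanced for each arm in expectation, and Table 1 already describes the comparator as matched.

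**Conclusion.** The point holds in limited form. The design matches on three variables, and the named primary analysis uses neither those variables nor the matched sets. Three consequences would follow if it were run as written:

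- 1:1 without reuse: somewhat conservative, losing about 3 to 13 power points for ρ between 0.1 and 0.3, and nothing at ρ = 0.
- Each control used twice: type I error of about 11% falling to about 6% as ρ goes from 0 to 0.3.
- Coarse fallback: residual age and duration imbalance left unadjusted, of a size the article does not allow one to compute.

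These figures assume the plan's difference and SD, 41 completers, two-sided 5%, and a value of ρ, a ratio and a reuse pattern that the article does not give. They do not show that the primary test is invalid, or that the authors intend an independent-groups analysis. Nor does accounting for matching rescue the sample size: 41 pairs reach 80% power only at ρ of about 0.73.

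**What to change.** Name the linear mixed model as the primary analysis in place of the open choice between two families. Include cohort, visit and cohort-by-visit, with sex, continuous age and continuous disease duration as covariates entered so that they act on the change as well as the level. Continuous terms also cover patients matched only through the fallback classes.

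Keep a matched-set identifier in the data set and cluster standard errors on the matched set, or on the historical individual if one serves several patients. State the matching ratio and whether reuse is allowed. A heavier structure, with random set-by-visit effects on top of these covariates, is not warranted with about 41 completers.

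For the descriptive comparison of each arm with EMSA-SG, use the controls matched to that arm's patients, so that Analysis sets and subgroups agrees with Table 1.

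The cost is a change of wording and one identifier, with no new patients or measurements. The downside is a few degrees of freedom, with no material gain if the matching variables turn out to be uninformative about change. The sample-size calculation needs its own correction.
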